### Study objectives

#### Primary aims

• Test the hypothesis that the use of CP during RSI in the ED does not prevent aspiration.

• Investigate the effect of CP on RSI and associated incidence of difficulty or failed intubation.

• Determine the incidence of pre-hospital aspiration.

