**Discussion:**

The benefits and risks of cricoid pressure application will be scrutinised by comparison of the incidence of aspiration and difficult or failed intubations in each group. The role of cricoid pressure in RSI in the emergency department and the use of a pepsin detection as a predictor of clinical aspiration will be evaluated.

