### Study design

This is a prospective randomised blinded controlled study of RSI and CP application within the ED. Due to ethical considerations, a control group without CP applied cannot be included in any study. Instead, this study will exploit the fact that the target range CP of 30 - 40 newtons (N) was applied only 25% of the time by ED staff when tested on a model larynx [29]. The incidence of aspiration (determined by pepsin detection in the trachea) in two groups of patients will be compared; those with conventional CP (and hence about a 25% chance of target range CP), and those with exact sustained target range CP (using weighing scales for direct biofeedback). Longitudinal follow-up of participants will be performed to determine to what degree detection of pepsin in the trachea correlates with the development of clinical aspiration syndromes. In addition the incidence of aspiration as a result of pre-hospital intubation (determined by pepsin detection in the trachea) will be determined.

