### Interventions

#### Intervention arm

The cricoid operator will stand on a set of scales with a visible display providing direct feedback of the force applied to the cricoid while performing CP. When required, the operator will apply 30 - 40 N force (equating to a weight displacement of 3.060 - 4.075 kg [29]) to the cricoid during RSI unless otherwise instructed by the intubation operator. Force will be applied until the endotracheal tube (ETT) placement is confirmed by end tidal CO_2 _and the ETT cuff is inflated.

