#### Control arm

The cricoid operator will stand on a set of scales while performing CP. The scale display will be covered to blind the operator to the amount of force they are using. When required, the cricoid operator will apply what they consider to be 30 - 40 N force to the cricoid during RSI unless otherwise instructed by the intubation operator. Force will be applied until the ETT placement is confirmed by end tidal CO_2 _and the ETT cuff is inflated.

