### Analysis

Continuous measurements will be expressed with means and standard deviations. Frequencies will be published the variables of interest. Two group comparisons will be undertaken using the Chi-squared test or Fisher's exact test where appropriate. Comparisons of means will utilise an independent *t *test. Ordinal and continuous variables will be compared using a Mann-Whitney test.

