## Discussion

The primary aim of this study is two-fold. Firstly, by comparing the incidence of aspiration of pepsin in the intervention and control groups and prospectively documenting the benefits and adverse events associated with 30 - 40 N of cricoid force during RSI, it aims to challenge the notion that CP prevents aspiration. Secondly, since the presence of pepsin in the oropharynx will be indicative of aspiration having occurred prior to intubation by virtue of the injury sustained by the patient, determining the incidence of pre-intubation aspiration will allow us to further evaluate the relevance of CP in the RSI algorithm in ED.

The secondary aim of this study is also two-fold. Firstly, defining any observed correlation between aspiration and pre-intubation Glasgow coma score will provide evidence for indications for the use of CP dependent upon the level of patient consciousness. Secondly, a correlation between detection of pepsin in trachea and development of aspiration syndromes will support the use of Fibrinogen plate assay in a clinical setting for their early detection and treatment.

It is conceivable that this research could also give rise to novel therapy. For example, once the incidence of serious aspiration and a pepsin positive assay is identified, the plate assay for pepsin could potentially be performed at the bedside, enabling doctors to treat aspiration pneumonia much earlier. It may also lead to amendments to the algorithm for RSI if CP is found to be deleterious.

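### The first primary aim asks whether cricoid pressure prevents aspiration, but both arms receive it, so the trial can only compare scale-guided with unmeasured pressure

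*Protocol article*

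**What the plan says.** Under Primary aims, the first item is to "Test the hypothesis that the use of CP during RSI in the ED does not prevent aspiration". The second is to investigate the effect of CP on rapid sequence intubation (RSI) and on difficult or failed intubation. The Discussion says of the arm comparison that "it aims to challenge the notion that CP prevents aspiration", and the abstract's discussion says that "The benefits and risks of cricoid pressure application will be scrutinised by comparison of the incidence of aspiration" and of difficult or failed intubations in each group.

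Study design states that "Due to ethical considerations, a control group without CP applied cannot be included in any study". It substitutes a proxy: patients given sustained target-range CP are compared with "those with conventional CP (and hence about a 25% chance of target range CP". In the intervention arm "the operator will apply 30 - 40 N force" with the display visible; in the control arm "the cricoid operator will apply what they consider to be 30 - 40 N force to the cricoid during RSI" with the display covered.

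Sample size assumes 11% aspiration in the control arm and 0% in the intervention arm, with 90% power and alpha 0.05, giving 106 per group. Analysis says "Two group comparisons will be undertaken using the Chi-squared test or Fisher's exact test where appropriate". The abstract's background gives a different first aim: to compare the ideal force with standard, unmeasured CP.

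**The concern.** The stated hypothesis is about CP against no CP. The randomised contrast is about how accurately CP is applied. An aim that the design does not address leads to conclusions that the data cannot carry.

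The hypothesis is also worded as an absence of effect, while the trial is sized to detect a difference and assumes that accurate CP abolishes aspiration. The aim as worded could be upheld only by finding no difference, and finding no difference between two ways of giving CP says nothing about leaving it out. The same gap affects the second aim: a difference in difficult intubation between the arms would describe guided against unguided CP, not CP itself.

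**Working it through.** **1. What the arm difference estimates.** Let *r* be the aspiration rate without CP, and *t*, *u* and *e* the rates with on-target, insufficient and excessive force. Background reports that staff tested on a model larynx were 25% on target, 47% insufficient and 28% excessive. Assume that these shares carry over to the control arm and that the guided arm is always on target.

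- Guided rate = *t*
- Control rate = 0.25*t* + 0.47*u* + 0.28*e*
- Control − guided = 0.47(*u* − *t*) + 0.28(*e* − *t*)

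The no-CP rate *r* does not appear. It enters only if a further assumption ties it to *u*, for example that insufficient force equals no CP.

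- If *u* = *r* and *e* = *t*, the difference is 0.47(*r* − *t*), which is the protective reading of the proxy.
- If *u* = *t* and *e* > *t*, the difference is 0.28(*e* − *t*), which is harm from excessive force with no protection shown. Background itself raises the possibility that CP promotes aspiration.
- If *t* = *u* = *e*, the difference is zero whether this common rate is far below *r* (CP works in both arms) or equal to *r* (CP does nothing).

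**2. The protocol's sample size.** Inputs from Sample size: 0.11 against 0, alpha 0.05 (taken as two-sided), power 90%; mean rate 0.055.

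n = [1.96·√(2×0.055×0.945) + 1.2816·√(0.11×0.89)]² / 0.11² = (0.632 + 0.401)² / 0.0121 ≈ 88.2, so 89.

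With continuity correction: (88.2/4)·[1 + √(1 + 4/(88.2×0.11))]² ≈ 105.6, so 106. The stated figure reproduces exactly, as a two-sided test for a difference.

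**3. What a null result would leave open.** 95% half-width for the difference with 106 per arm and equal rates:

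- 11% in both arms: 1.96·√(2×0.11×0.89/106) = 0.084. The interval excludes 11 points but not a fall from 11% to 11 − 8.4 = 2.6%.
- 22% in both arms (the upper rate quoted in Sample size): 1.96·√(2×0.22×0.78/106) = 0.112. This does not exclude even an 11-point effect.

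Two-sided power at 106 per arm (normal approximation without continuity correction; Fisher's exact in brackets):

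| Control vs guided | Power |
|---|---|
| 11% vs 0% | 94.5% (98%) |
| 11% vs 4% | 49% (40%) |
| 11% vs 5.5% | 31% (23%) |

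A halving of aspiration would be missed about seven times in ten.

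**4. Would more patients help?** The documents give no margin, so these are illustrations. To rule out a benefit of guided force as large as *m*, with 11% in both arms, 90% power and one-sided 2.5%: n = 2×0.11×0.89×(1.96 + 1.2816)²/*m*². This gives 171 per arm for *m* = 11 points and 681 for *m* = 5.5 points. Both exceed 106, and either trial would still compare two forms of CP.

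**The case against.** The protocol is open about the missing no-CP arm and offers a reasoned substitute. It says that 30–40 N is generally accepted as sufficient to occlude the oesophagus and that nearly half of staff pressed too lightly. On those premises the arms differ in how much effective CP they receive, and less aspiration in the guided arm would be evidence against the claim that CP does nothing. Stating a null hypothesis and powering a trial to reject it is ordinary practice. This much stands: it would be too strong to say that the trial has no bearing on the hypothesis. The inference works in one direction only, and off-target harm remains a rival explanation.

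Three stronger readings are tempting, and the documents do not support them.

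- A reader might infer that the plan treats a non-significant test as proof that CP is useless. No decision rule of that kind is stated; the aim and the Discussion invite the reading but do not prescribe it.
- A reader might infer that a null result would lead to changes in the RSI algorithm. The Discussion makes such changes conditional on CP being found deleterious.
- A reader might count the absence of an effect estimate and interval from Analysis as a fault. A condensed article can leave that to an analysis plan that is not shown.

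A null result would also not be empty: at 11% in both arms it would speak against the protocol's own premise that accurate force removes an 11% risk.

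**Conclusion.** The first primary aim, and the parts of the second aim and the Discussion that speak of CP itself, do not match the randomised contrast. This is an inconsistency within the article, which an analysis plan could not remove because it lies between the aim and the arms. The comparison of guided with unmeasured CP remains valid.

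Similar rates in the two arms could not support the stated hypothesis at any sample size. At the planned size they would also leave open a substantial benefit of accurate force: ±8.4 points if both arms show 11%, ±11.2 points if both show 22%. These half-widths assume complete data on 106 patients per arm and a normal approximation. The algebra assumes that the model-larynx shares apply in practice. Staff education teaches delivery of 30–40 N to all staff, and Background says training helps in the short term, so the contrast in force may be smaller, and a null result would then say even less.

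**What to change.** - Restate the first primary aim as whether scale-guided 30–40 N CP reduces aspiration compared with unmeasured CP, in line with the abstract's background.
- Tie the restated aim to the trial's primary outcome once that is reconciled. The abstract's methods count oropharyngeal or tracheal pepsin, or treatment for aspiration pneumonitis; Outcome measures lists tracheal pepsin and treatment as primary and oropharyngeal pepsin as secondary. The new wording should not settle that difference silently.
- Limit the second aim and the related claims in the Discussion to guided against unguided CP.
- State that a non-significant difference will not be taken as evidence that CP does not prevent aspiration, and report the risk difference with its 95% confidence interval so that readers can see what remains open.
- If a conclusion of no difference is wanted, give a justified margin and a matching sample size, and still confine it to the two ways of applying CP.

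Apart from that last option, the arms, sample size, data collection and tests are unchanged. The cost is wording, one interval and a narrower claim.

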#### Secondary aims

• Determine whether a relationship exists between the incidence of aspiration and pre-intubation Glasgow coma score (GCS).

• Determine any correlation between pepsin detection in aspirates and development of clinical aspiration syndromes.

### Setting

Three hospitals will participate in the trial: Tamworth Rural Referral Hospital (Hunter New England Local Health District), and Port Macquarie and Coffs Harbour Base Hospitals (Mid North Coast Local Health District).

### Participants

Adult patients (> 18 years) undergoing RSI in the ED will be invited to participate in the study. Patients will be randomised to receive either standard CP (Control arm) or sustained "ideal" CP (Intervention arm). Patients will be excluded from the trial if cardiopulmonary resuscitation (CPR) is in progress upon arrival at the ED.

### Consent

Consent will be sought from the patient (or their Next of Kin) to participate in the trial, for testing the endotracheal and oropharyngeal aspirates for pepsin and for the 28 day follow-up. The right to refuse is clearly stated on the consent form. Patient consent is sought by the CP operator. In instances where a relative consents for the trial, participant consent is sought as soon as practicable after they have been successfully intubated and stabilised.

The study protocol has been approved by both the Hunter New England Human Research Ethics and the North Coast Area Health Service Human Research Ethics Committees.

### Randomisation

Patients will be randomised to the treatment groups by a directive included in the enrollment pack which is not apparent until the pack is opened to ensure all staff members are blinded to the participant's group allocation.

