### Methods

#### Cricoid pressure measurement

A platform scale with pole-mounted liquid crystal display LCD (150 kg capacity) set to record in 0.01 kg increments is used to measure cricoid pressure (Figure 1. Model PT270, PT Global Pty Ltd., NSW, Australia). The scale is mounted on a hand trolley with a custom made extended toe plate (designed to support the base plate of the scale without interfering with its levelling feet) allowing it to be easily manoeuvred into position next to the resus bed when required. Once in position and turned on, the cricoid operator stands on the scale and select the tare option to display their body weight as zero. Direct feedback of the force applied to the cricoid is available via the displayed weight reduction (a reading of -1 kg equates to approximately 10 N force). The cricoid operator maintains contact only with the scale baseplate and the patient's cricoid cartilage during the procedure to ensure the weight displayed accurately reflects the amount of their body weight transferred through the patient's cricoid.

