### Data collection

After the intubation is complete the personnel involved complete a data sheet included in the trial enrollment pack. Data recorded includes patient demographics, procedural details, procedural and post-intubation complications encountered.

*Patient demographic details*; age, date & time of intubation and medical record number (for 28 day follow-up).

*Procedural details*; location of intubation (ED or pre-hospital), lowest pre-intubation GCS, intubation drugs used, experience of intubation operator, evidence and nature of macroscopic aspirate seen and grade of laryngoscopic view obtained.

*Procedural complications*; 3 or more attempts to place the ETT in the trachea, > 10 minutes using conventional laryngoscopy, required change of operator, termination of the attempt at RSI, use of laryngeal mask or surgical airway.

*Post-intubation complications encountered within 30 minutes of RSI*; severe hypotension (Systolic blood pressure < 60 mmHg), severe hypoxaemia (SaO_2 _< 70%), death and cardiac arrest.

The data sheet and SD card containing weight data will be sent to the Trial Coordinator who will enter the data into a password-protected database. Each episode of RSI has a unique randomly assigned number within the database (Plate Number). This number will be linked to the episode of service, and the pepsin assay result will be automatically appended to the corresponding patient data set in the database. The investigators are therefore blinded to the results coming in from the laboratory.

At 28 days the patient notes will be reviewed. The acute physiology and chronic health evaluation (APACHE II) score and diagnostic code will be determined and any treatment for aspiration as an inpatient (discharge diagnosis of aspiration pneumonitis/pneumonia or antibiotic therapy explicitly instituted to treat for aspiration pneumonia) will be noted.

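### The protocol presents allocation concealment as blinding of all staff, but the cricoid operator must know the arm, and the judgement-based bedside outcomes and the 28-day review have no stated masking

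*Protocol article*

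**What the plan says.** Study design states: "This is a prospective randomised blinded controlled study of RSI and CP application within the ED". It does not say who is blinded.

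Randomisation says the directive in the enrolment pack is "not apparent until the pack is opened to ensure all staff members are blinded" to group allocation.

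The two arms differ in the state of the scale display. In the intervention arm, "The cricoid operator will stand on a set of scales with a visible display providing direct feedback". In the control arm, "The scale display will be covered to blind the operator to the amount of force they are using". Cricoid pressure measurement describes a pole-mounted display on a trolley, "allowing it to be easily manoeuvred into position next to the resus bed when required".

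Data collection then states: "After the intubation is complete the personnel involved complete a data sheet included in the trial enrollment pack". That sheet carries the grade of laryngoscopic view, the procedural complications and the complications within 30 minutes. The same section has the notes reviewed at 28 days for treatment of aspiration. It blinds the investigators to incoming laboratory results. Sample processing blinds each laboratory to how cricoid pressure was conducted.

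**The concern.** Hiding an assignment until a pack is opened is allocation concealment. It protects against selective enrolment. It does not blind anyone during or after the procedure, because the pack has to be opened before the display can be left visible or covered. The document therefore claims a property for the trial that its own procedures remove.

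Two things are at stake. A report that repeats the label would tell readers that all staff were blinded when at least one member of the team could not be. In addition, difficulty or failure of intubation is a primary aim, and the Discussion part of the abstract says benefits and risks will be judged partly on it. Some items that inform it depend on judgement or discretion at the bedside, where knowledge of the arm can affect what is done or written down.

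**Working it through.** **Who knows the arm, role by role**

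| Role | What the protocol says | Masked to arm? |
|---|---|---|
| Cricoid operator, intervention | Reads the force on a visible display | No, necessarily |
| Cricoid operator, control | Stands on the scale with the display covered; told to aim for the same range unaided | No; blinded to force, not to arm |
| Intubation operator | May instruct changes to cricoid pressure; sight of display and directive not described | Not stated; exposure probable, since the display is on a pole at the bedside |
| Whoever completes the data sheet | Personnel involved in the intubation; the sheet comes in the pack that also holds the directive | Not stated; exposure probable |
| Laboratory | Blinded to conduct of cricoid pressure | Yes |
| Investigators | Blinded to laboratory results | Not stated for arm |
| 28-day notes reviewer | Not described | Not stated |

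The first two rows are enough to make the all-staff claim untrue. The rows marked probable are inferences.

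**Which outcomes are exposed**

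- *Protected:* pepsin in tracheal and oropharyngeal aspirates, read by a blinded laboratory.
- *Less vulnerable:* three or more attempts, more than 10 minutes, use of a laryngeal mask or surgical airway, systolic pressure below 60 mmHg, saturation below 70%, cardiac arrest and death. These are counts, thresholds or plain events.
- *Exposed:* grade of laryngeal view, which is a judgement, and change of operator and termination of the attempt, which are discretionary acts even though recording them is straightforward.
- *Unprotected as written:* treatment for aspiration, listed under primary outcome measures. It depends on a notes review that looks for a discharge diagnosis or antibiotics explicitly started for aspiration.

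**The protocol's own figure.** The sample size is not affected by this point. It reproduces from 11% against 0%, 90% power and two-sided 5%:

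- Uncorrected: n = [1.960·√(2 × 0.055 × 0.945) + 1.2816·√(0.11 × 0.89)]² / 0.11² = 88.2, which rounds up to 89.
- With continuity correction: (88.2/4)·[1 + √(1 + 4/(88.2 × 0.11))]² = 105.6, which rounds up to the stated 106 per arm.

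**Illustration of scale, on assumed values.** The document gives no figure for recording bias. Suppose a binary bedside outcome has the same true rate p in both arms, and unblinded recording lowers the recorded rate in one arm by s. With n = 106 per arm, p̄ = p − s/2, se₀ = √(2p̄(1 − p̄)/n) and se₁ = √([p(1 − p) + (p − s)(1 − p + s)]/n):

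chance of a false significant result = 1 − Φ((1.96·se₀ − s)/se₁) + Φ((−1.96·se₀ − s)/se₁)

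| Assumed base rate | s = 3 points | s = 5 points |
|---|---|---|
| 10% | 12.2% | 28.1% |
| 20% | 8.7% | 15.9% |
| 30% | 7.7% | 12.9% |

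For p = 10% and s = 3 points, se₀ = 0.0383 and se₁ = 0.0383, so the two tails are 0.119 + 0.003 = 0.122. The nominal figure is 5%. The table shows only that a shift of a few points would matter at this sample size. It is not evidence that such a shift occurs.

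**The case against.** The strongest reply is that the error is one of wording and the bias is conjecture. The protocol does not say which way the display faces, who opens the directive or who enters the view grade, and a journal article may leave such details to the full protocol. Most recorded complications are counts or thresholds. Both arms receive cricoid pressure aimed at 30–40 N, so a belief that cricoid pressure obscures the view does not by itself favour either arm. Applied force is logged at 60 points per second in both arms, so any change in pressure that the intubator requests is on record. The pepsin outcome, on which the sample size was argued, is read blind.

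Much of this stands. A reader might infer that the whole team, including whoever grades the view, is known to be unblinded, and that the entire intubation-difficulty aim is compromised. The text supports neither. Exposure beyond the cricoid operator is a likely consequence of the set-up rather than a stated fact, and the vulnerable items are a minority. The lack of a stated direction also stands, as does the value of the force log, although a log shows what force was applied and does not protect the view grade.

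The objection does not rescue the claim itself. That all staff are blinded is an affirmative statement, not an omitted detail, and no fuller document can make it true while the cricoid operator works with a display whose state defines the arm.

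**Conclusion.** The point holds in a limited form. It is certain from the text that Randomisation mislabels concealment as blinding of all staff, that Study design repeats the label without qualification, and that the cricoid operator cannot be blinded to arm. It is probable, but not stated, that others at the bedside can tell the arm. If they can, laryngeal view grade, change of operator and termination of the attempt are open to arm-related bias of unknown direction. The 28-day review is a weaker matter: masking is not stated, and the full protocol may provide it.

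The size of any bias cannot be derived from the document. The false-positive figures above rest wholly on assumed base rates and shifts. Nothing here touches the pepsin result or the sample size. The change should be made, but it does not put the pepsin comparison in doubt.

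**What to change.** 1. In Randomisation and Study design, replace the blinding claim with wording such as: allocation concealed until the pack is opened; cricoid operator not blinded to arm; laboratory blinded. Drop the statement that all staff are blinded.
2. In both arms, turn or shield the display so that only the cricoid operator can see whether it is covered, and let only that operator open the directive.
3. Have the intubation operator record the view grade and the discretionary items on a separate sheet that does not show the allocation.
4. Keep the 28-day notes reviewer unaware of the arm, and say so.

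The first change costs nothing. The others use existing equipment and need no extra staff, but forms and staff instructions need a minor update at three hospitals. Because the trial is ongoing, the date of the change should be recorded, since bedside items will have been collected under different conditions before and after it. Masking in a resuscitation bay may be imperfect, and masking the notes reviewer protects the abstraction of treatment, not the treatment decision itself.
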